#### 4.4 control

Participants in the control group will receive a brochure with locally available non-clinical support services, which will be sent to the participants by the study nurse after randomization to the control group.

This process is described in the *SocPres\_SOP Implementation of the intervention* is described in detail.

#### 4.5 measures to reduce bias

##### 4.5.1 Randomization and Allocation

Randomization in this study is done to test the feasibility of randomization for the main confirmatory study. That is, randomization is not done with the aim of testing comparative hypotheses.

The randomization code is created by an independent person from the Institute of Social Medicine, Epidemiology and Health Economics (who is not otherwise involved in the study) as a block randomization (with variable block length) stratified by study center (general practitioner's practice) with an allocation ratio of 2:1.

All patients who consent to participate and meet the inclusion criteria will be randomized after the baseline assessment. The randomization codes will be taken from the REDCap database by the study

|                                  |                                   |                                                                                                         |                 |
|----------------------------------|-----------------------------------|---------------------------------------------------------------------------------------------------------|-----------------|
| Version: V1.2                    | Last review:
February 12, 2025 | Created: [name], [name], [name], [name], [name] | Page
22of 52 |
|                                  |                                   | Reviewed by: [name], [name]                                                    |                 |
| Release on:
February 12, 2025 | Next check:
N/A                | Released: [name]                                                                       |                 |
|                                  |                                   | Valid from: 04.09.2024                                                                                  |                 |

|                   |                          |                                                                 |  |
|-------------------|--------------------------|-----------------------------------------------------------------|--|
| study
protocol | Study: „Soziales Rezept“ | Campus:
CCM                                                  |  |
|                   |                          | Scope:
Institute for General Practice and
Family Medicine |  |

nurse responsible for allocation , with allocation to the next patient being concealed . Allocation will therefore take place without any influence from the study management, the investigators or the link workers .

The procedure is described in the *SocPres\_SOP Randomization and Allocation* .

#### 4.5.2 blinding

Due to the study design, blinding of the investigators , link workers and patients is not possible. Due to the 2:1 randomization, blinding of the statistical analyses is also not possible.

#### 4.6 study participants and centers

For the study , 300 adult patients with non-medical health-related problems (see section 4.5.2) will be recruited by their treating general practitioners . Recruitment will take place in nine study centers.

##### 4.6.1 Inclusion and exclusion criteria for trial centers

Inclusion criteria: The principal investigator of the respective study center (general practitioner's practice) has the following qualifications:

- General practitioner ( specialist in General Practice and Family Medicine or internal medicine with primary care, general practitioner doctor )
- 80 hours of basic training in "Psychosomatic Basic Care"

Exclusion criteria:

- Practices with more than 50% of their care volume in specialized care (e.g. specialized outpatient palliative care, infectious diseases, addiction therapy, psychotherapy)

The inclusion and exclusion criteria at practice level are intended to ensure generalisability to primary care.

##### 4.6.2 Inclusion and exclusion criteria for patients

Inclusion criteria:

- patients (18 years and older) who are capable of consenting
- Presence of one or more non-medical health-related social problems (see below)

Exclusion criteria:

|                                  |                                   |                                                                                                         |                  |
|----------------------------------|-----------------------------------|---------------------------------------------------------------------------------------------------------|------------------|
| Version: V1.2                    | Last review:
February 12, 2025 | Created: [name], [name], [name], [name], [name] | Page
23 of 52 |
|                                  |                                   | Reviewed by: [name], [name]                                                    |                  |
| Release on:
February 12, 2025 | Next check:
N/A                | Released: [name]                                                                       |                  |
|                                  |                                   | Valid from: 04.09.2024                                                                                  |                  |

|                |                          |                                                              |  |
|----------------|--------------------------|--------------------------------------------------------------|--|
| study protocol | Study: „Soziales Rezept“ | Campus:
CCM                                               |  |
|                |                          | Scope:
Institute for General Practice and Family Medicine |  |

- patients who are legally cared for in relation to health
- a person living in the same household is already included in the study

Non-medical health-related social problems are defined by chapter ZC of the International Classification of Primary Care – 3rd Revision (ICPC-3) (8) .

The classification includes problems in the following areas:

- Financial problems (including poverty)
- Problems with social benefits (including lack of receipt of social benefits, problems with incapacity to work)
- problems at work
- Unemployment as a problem
- loneliness, social isolation
- Problems in the relationship with a partner, with a child, with parents or other family members, with other people (including bullying)
- Loss/death of a partner, child, parent or other family member
- Problems due to the illness of a partner, child, parent or other family member
- Problems related to education, school, training, or studies (including illiteracy, lack of school qualifications)
- problems due to discrimination
- Problems due to residence status/residence permit
- problems with experiences of violence
- housing problems (including homelessness or threatened homelessness)
- Legal problems (e.g. threatened prison sentence or similar)
- Problems with the health system (e.g. care
- Other social problems

## 4.7 patient pathway and visits

The visit overview in Table 4 and the CONSORT flow diagram (Figure 2) show the individual patient path through the study. The individual time points from Table 4 are described below.

|                                  |                                   |                                                                                                         |                  |
|----------------------------------|-----------------------------------|---------------------------------------------------------------------------------------------------------|------------------|
| Version: V1.2                    | Last review:
February 12, 2025 | Created: [name], [name], [name], [name], [name] | Page
24 of 52 |
|                                  |                                   | Reviewed by: [name], [name]                                                    |                  |
| Release on:
February 12, 2025 | Next check:
N/A                | Released: [name]                                                                       |                  |
|                                  |                                   | Valid from: 04.09.2024                                                                                  |                  |

|                |                          |                                                              |  |
|----------------|--------------------------|--------------------------------------------------------------|--|
| study protocol | Study: „Soziales Rezept“ | Campus:
CCM                                               |  |
|                |                          | Scope:
Institute for General Practice and Family Medicine |  |

Table 4: Visit overview

| visit                                      | t -1              | t 0                | s 1            | s 2 , s 3 , ..., s n | t 1    | t 2    |
|--------------------------------------------|------------------------------|-------------------------------|---------------------------|-------------------------------------------------------|-------------------|-------------------|
|                                            | consultation in the practice | baseline survey/randomization | First Link Worker Session | Follow up Link Worker sessions                        | 3-month follow-up | 6-month follow-up |
| inclusion                           |                              |                               |                           |                                                       |                   |                   |
| review of inclusion and exclusion criteria | X                            |                               |                           |                                                       |                   |                   |
| enlightenment                              | X                            |                               |                           |                                                       |                   |                   |
| consent                                    | X                            |                               |                           |                                                       |                   |                   |
| Sociodemographic data                      |                              | X                             |                           |                                                       |                   |                   |
| randomization                              |                              | X                             |                           |                                                       |                   |                   |
| treatment per study arm             |                              |                               |                           |                                                       |                   |                   |
| TAU+ (brochure)                            |                              | X                             |                           |                                                       |                   |                   |
| Social prescribing                         |                              | X                             | X                         | X                                                     | X                 | X                 |
| survey instruments                  |                              |                               |                           |                                                       |                   |                   |
| feasibility endpoints                      | X                            | X                             | X                         | X                                                     | X                 | X                 |
| WHODAS 2.0                                 |                              | X                             |                           |                                                       | X                 | X                 |
| WHO-5                                      |                              | X                             |                           |                                                       | X                 | X                 |
| L-1                                        |                              | X                             |                           |                                                       | X                 | X                 |
| ICECAP-A                                   |                              | X                             |                           |                                                       | X                 | X                 |
| EQ-5D-5L                                   |                              | X                             |                           |                                                       | X                 | X                 |
| De Jong Gierveld Loneliness Scale          |                              | X                             |                           |                                                       | X                 | X                 |
| Target-based endpoint (intervention arm)   |                              |                               | X                         |                                                       | X                 | X                 |
| utilization behavior (PECUNIA-RUM)         |                              | X                             |                           |                                                       | X                 | X                 |

|                                  |                                   |                                                                                                         |                  |
|----------------------------------|-----------------------------------|---------------------------------------------------------------------------------------------------------|------------------|
| Version: V1.2                    | Last review:
February 12, 2025 | Created: [name], [name], [name], [name], [name] | Page
25 of 52 |
|                                  |                                   | Reviewed by: [name], [name]                                                    |                  |
| Release on:
February 12, 2025 | Next check:
N/A                | Released: [name]                                                                       |                  |
|                                  |                                   | Valid from: 04.09.2024                                                                                  |                  |

|                   |                          |                                                                 |  |
|-------------------|--------------------------|-----------------------------------------------------------------|--|
| study
protocol | Study: „Soziales Rezept“ | Campus:
CCM                                                  |  |
|                   |                          | Scope:
Institute for General Practice and
Family Medicine |  |

|                          |  |   |   |   |   |   |
|--------------------------|--|---|---|---|---|---|
| Subjective health status |  | X |   |   | X | X |
| Security                 |  | X | X | X | X | X |

|                                  |                                   |                                                                                                         |                  |
|----------------------------------|-----------------------------------|---------------------------------------------------------------------------------------------------------|------------------|
| Version: V1.2                    | Last review:
February 12, 2025 | Created: [name], [name], [name], [name], [name] | Page
26 of 52 |
|                                  |                                   | Reviewed by: [name], [name]                                                    |                  |
| Release on:
February 12, 2025 | Next check:
N/A                | Released: [name]                                                                       |                  |
|                                  |                                   | Valid from: 04.09.2024                                                                                  |                  |

|                |                          |                                                              |  |
|----------------|--------------------------|--------------------------------------------------------------|--|
| study protocol | Study: „Soziales Rezept“ | Campus:
CCM                                               |  |
|                |                          | Scope:
Institute for General Practice and Family Medicine |  |

[figure not shown]

Abbildung 2: CONSORT-Flussdiagramm

#### 4.7.1 t-1 : consultation in the practice

1. The starting point is when a non-medical health-related social problem is raised in a normal doctor-patient consultation with one of the investigators in one of the trial centers. Such problems can be, for example:

- loneliness
- financial problems
- problems at work

|                                  |                                   |                                                                                                         |                  |
|----------------------------------|-----------------------------------|---------------------------------------------------------------------------------------------------------|------------------|
| Version: V1.2                    | Last review:
February 12, 2025 | Created: [name], [name], [name], [name], [name] | Page
27 of 52 |
|                                  |                                   | Reviewed by: [name], [name]                                                    |                  |
| Release on:
February 12, 2025 | Next check:
N/A                | Released: [name]                                                                       |                  |
| Valid from: 04.09.2024           |                                   |                                                                                                         |                  |

|                |                          |                                                              |  |
|----------------|--------------------------|--------------------------------------------------------------|--|
| study protocol | Study: „Soziales Rezept“ | Campus:
CCM                                               |  |
|                |                          | Scope:
Institute for General Practice and Family Medicine |  |

- problems in the family
  - problems with the apartment/living space
2. In this case, the investigator can offer the patient participation in the study. The investigator informs the patient about the study and documents this in his investigator-specific recruitment list.
  3. If the patient is interested in participating in the study, the investigator checks the study's inclusion and exclusion criteria and provides verbal and written information about the study using the study information. The patient is given a participant information sheet.
  4. The patient is given as much time to think about it as he or she wants. This means that he or she can give his or her consent directly during this consultation or at a later date.
  5. If the patient agrees to participate, the patient and the investigator sign the consent form in duplicate. The original remains at the trial center. The patient receives the second copy of the signed consent form.
  6. The data of the included patients are then transmitted by the investigator to the Charité. Various secure transmission channels are available.

The details of the procedures at t-1 are described in detail in the *SocPres\_SOP practice consultation*.

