| endpoints | 
Primary feasibility endpoints:
 
Proportion of participants who have at least one appointment with the link worker (intervention arm only)
 
Proportion of participants who discontinue the study before 6 months of follow-up (loss to follow- up , both arms)
 
Secondary feasibility endpoints:
 
Acceptance:
 
Satisfaction with the intervention among general practitioners ( last patient last visit questionnaire ) and
 
participant satisfaction (3-month follow-up and 6-month follow-up)
 
Practicability:
 
Estimated time required by general practitioners
 
Proportion of eligible patients compared to the number of patients treated in the practice
 
Proportion of patients who were excluded due to a language barrier
 
Proportion of eligible patients who consent to the study
 
Proportion of consenting patients who are randomized
 
Proportion of randomized patients who attend scheduled appointments with the link worker (intervention arm only)
 
Need/Use (intervention arm only):
 
From GP: assessed need for SP of participants
 
Participants' SP needs assessed by Link Worker
 
Number of appointments with link workers per participant
 
Duration of appointments with link workers
 |

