|                                                                                                                | Proportion of eligible patients compared to the number of patients treated in the practice                                                         |
|                                                                                                                | Proportion of patients who were excluded due to a language barrier                                                                                 |
|                                                                                                                | Proportion of eligible patients who consent to the study                                                                                           |
|                                                                                                                | Proportion of randomized participants who attend appointments agreed with link workers (intervention arm only)                                     |
| Determination of needs and use                                                                                 | From GP: assessed need for SP of participants (intervention arm only)                                                                              |
|                                                                                                                | Participants' SP needs assessed by link worker (intervention arm only)                                                                             |
|                                                                                                                | Number of consultations with Link Worker per participant (intervention arm only)                                                                   |
|                                                                                                                | Duration of consultations with link workers (intervention arm only )                                                                               |

|                                  |                                   |                                                                                                         |                  |

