#### 6.1.4 recruitment list

The information relevant to the feasibility endpoints in the recruitment lists completed by the investigators is regularly queried by the Charité.

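### Criteria are checked only after a patient shows interest, so the count of eligible patients behind two feasibility endpoints is not established for those who decline at once or are not offered the study

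*Protocol*

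**What the plan says.** Section 4.7.1 sets the order at the practice consultation. Once a social problem comes up, step 2 leaves the offer to the doctor: "In this case, the investigator can offer the patient participation in the study". The same step creates the record: "The investigator informs the patient about the study and documents this in his investigator-specific recruitment list". Step 3 then makes the check conditional: "If the patient is interested in participating in the study, the investigator checks" the inclusion and exclusion criteria. Time to consider and the consent decision follow in steps 4 and 5. The visit overview (Table 4) places the criteria review at t-1 only, so no later visit fills the gap.

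Table 2 in section 3 has two practicability endpoints that need a count of eligible patients: "Proportion of eligible patients who consent to the study" and "Proportion of eligible patients compared to the number of patients treated in the practice". In the first, eligible is the denominator; in the second, it is the numerator. The protocol does not define eligible for either.

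Section 6.1.4 names the data source: "The information relevant to the feasibility endpoints in the recruitment lists completed by the investigators is regularly queried by the Charité".

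The synopsis (section 1.6) plans 600 screened, 300 recruited and 215 randomized, with 150 to 215 analysed. It also lists "Proportion of consenting patients who are randomized", a line that Table 2 does not carry.

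**The concern.** The two proportions are recruitment inputs for the confirmatory trial, and supplying such inputs is part of the study's main objective. Both need eligibility to be known whether or not the patient wants to take part. The stated order makes it known only for patients who do.

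Two groups are affected, in different ways. Patients who refuse at once are on the list but unassessed. Patients whom the doctor chooses not to approach have no described record at all. The first group distorts the consent proportion if it is dropped from the denominator. Both groups lower the eligible-to-treated proportion, which then partly reflects each doctor's habits in offering the study.

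The SAP is not at hand and may define eligible. It cannot, however, supply an assessment that the protocol does not require anyone to make, and that assessment cannot reliably be reconstructed afterwards.

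**Working it through.** **The plan's own figures.** These reproduce. At 30% dropout, 215 × 0.7 = 150.5, by arm 143 × 0.7 = 100.1 and 72 × 0.7 = 50.4, against the stated 150, 100 and 50. The plan states no consent proportion. The planned counts imply 300/600 = 50.0% from screening to recruitment and 215/300 = 71.7% from recruitment to randomization, a loss of 85 patients (28.3%).

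**Notation.** E is the number of truly eligible patients with a social problem raised, g the share of them never offered the study, f the share of those offered who show no interest, C the number consenting, and T the number treated in the practice. The protocol gives neither f nor g, so both are assumptions.

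**Direction.** Nobody consents without interest, so C is the same on either count. If eligible means having passed the step 3 check:

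- Reported consent proportion = C / [offered eligible × (1 − f)] = (true proportion among offered) / (1 − f). This is never below the true value.
- Reported eligible-to-treated = (E/T) × (1 − f) × (1 − g). This is never above the true value.

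**Size, case A.** Assume that the 600 are all offered and eligible, and that 300 consent, so the true proportion is 50.0%.

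| f (assumed) | Checked = 600(1 − f) | Reported = 300/checked |
|---|---|---|
| 10% | 540 | 55.6% |
| 20% | 480 | 62.5% |
| 25% | 450 | 66.7% |
| 30% | 420 | 71.4% |
| 40% | 360 | 83.3% |

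**Size, case B.** Assume instead that the 600 are only those who were checked and found eligible. The reported figure is then 50.0%, and the proportion among all offered is 50% × (1 − f): 45.0%, 37.5% and 30.0% at f = 10%, 25% and 40%. If g = 25% were also never offered, multiplying by 0.75 gives 33.8%, 28.1% and 22.5% of all eligible patients.

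**Eligible-to-treated.** With g = 0, the reported value is 0.90 to 0.60 of the true one for f = 10% to 40%. With g = 25%, it is 0.675 to 0.45 of it.

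**The case against.** The strongest reply has four parts.

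**Refusers are not lost.** Step 2 logs every informed patient before interest is known, and section 6.1.4 makes the list a source for the feasibility endpoints. Consented over informed can therefore be formed. Patients who show interest, pass the check and then decline also stay in the denominator. This stands. A reader might infer that everyone who declines drops out of the denominator, but the documents do not support that: only immediate refusers lack an assessment, and even they are listed.

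**Most of eligibility is known already.** The social problem is the entry point to the process, and section 4.6.2 adds little beyond adulthood, capacity to consent, no legal guardianship in health matters and no household member already enrolled. The listed count may therefore be close to the eligible count. That is fair, but the protocol does not say that listed patients are to be counted as eligible, and it reserves the criteria check for the interested.

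**Other documents may settle it.** The practice-consultation SOP, the list template and the CONSORT figure are not visible, and defining endpoints is ordinary SAP content. The separate endpoint on language barriers, which is not an exclusion criterion in section 4.6.2, hints that more may be recorded. This limits how firmly the bias can be asserted. But an SOP that assessed every offered patient would depart from the order in section 4.7.1.

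**The size is assumed.** This stands as well. A reader might infer that the consent proportion will come out at 63% to 83%, or that a later trial would under-plan screening by 20% to 40%. Both need an assumed interest share of 60% to 80% and an assumed meaning of screening, which the protocol does not define. The second also needs planners to apply a proportion conditional on interest to all offered patients, although the list would give them the unconditional one.

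**Conclusion.** The concern holds as a defect in the order of data capture. Following section 4.7.1, eligibility is not established for immediate refusers, and no record is described for patients not offered the study. On the natural reading of eligible as having passed the check, the direction is certain: the consent proportion is too high whenever any eligible offered patient is uninterested, and the eligible-to-treated proportion is too low. The documents do not fix the amount. The 56% to 83% against a true 50% is an illustration that rests on 600 offered and eligible patients, 300 consents and an assumed 10% to 40% uninterested.

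If all listed patients are counted instead, the upward bias goes. The result is then consented over informed, which includes people whose eligibility was never checked and still leaves out those not offered the study.

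The missing Table 2 line on consenting patients who are randomized is editorial. A reader might infer that the endpoint was dropped, but the synopsis still plans it and the described process yields both counts.

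**What to change.** 1. In section 4.7.1 and the practice-consultation SOP, move the basic criteria check ahead of the question of interest.
2. For every patient entered in the existing recruitment list, record criteria met (y/n), interested (y/n) and consented (y/n).
3. Define eligible for both endpoints from that entry, irrespective of interest.
4. Report interested over eligible and consented over eligible separately. Report patients listed before the change separately.
5. Where feasible, add a simple count of patients who raised a social problem but were not offered the study. Otherwise, state that eligible-to-treated is a lower bound that depends on each doctor's offering practice.
6. Align Table 2 with the synopsis (editorial).

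Items 1 to 4 cost a few tick-boxes per listed patient. Item 5 is optional because it costs more: it reaches beyond the list, and the protocol itself describes such problems as common in primary care.
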